### Sample size calculations

The sample size calculation is based on the primary outcome measure, the WOMAC score at 12-month. Based on previous studies, [5, 16, 17, 25] a 11.5 points reduction in WOMAC total score was considered as the minimum difference to be detected between the groups with a standard deviation (SD) of 16. Accepting a false-positive rate of 5% (α = 0.05) and a power of at least 90% (β = 0.10), we determined a theoretical minimum sample size of 84 patients. Considering the estimated 15% dropout rate, a total of 50 patients per group were required. Patient recruitment will be terminated in both groups when the required minimum number of patients is attained.

### Data management

Paper-based questionnaires will be the primary data collection tools for the study. The questionnaires will be completed at the outpatient clinic at baseline and each follow-up time point. On receipt of the questionnaire forms, the coordinating researchers will make a visual check of the responses and query missing data when possible. The paper-based questionnaire will be securely kept by a study nurse.

A study nurse, blinded to the group allocation, will store the forms into an electronic database by double data entry to minimise typing errors. The coordinating researchers, blinded to the group allocation, will perform a visual check of the data in the electronic database and then query all missing, implausible and inconsistent data. Patient records in the participating hospitals will be used when collecting missing data or interpreting inconsistent or implausible data.

After 12-month follow-up visits are completed and all data stored, a research assistant, not involved in the trial, will aggregate all the data into a separate database, which will be the source for the final data analysis. Participant files will be maintained in storage (both in electronic and paper formats) at the coordinating center for a period of 10 years after completion of the study (10-year follow-up visits).

### Statistical analysis

We will conduct an intention-to-treat analysis whereby all participants will be included in the study in the group to which they were randomized. The analysis will be conducted by a statistical expert blinded to the trial, with two-sided hypothesis tests and *p*-values < 0.05 significant.

Baseline characteristics will be analyzed between groups using descriptive statistics. Continuous variables will be expressed in terms of the means and the standard deviations, and compared using the student t test (normally distributed) or Mann-Whitney U test (nonnormally distributed). The categorical data will be expressed as frequency and compared using the Chi-square test or Fisher’s exact test. Normality will be confirmed using the Kolmogorov-Smirnov test.

### Primary outcomes analysis

To test for the effect of treatment on the between-group difference in the primary outcome (WOMAC score), we will use a repeated measurement general linear model (GLM) with Sidak test for multiple comparisons. Changes from baseline to all follow-up time points (1-, 3-, 6- and 12-month) will be included in the model to assess the differences in the primary outcome at different follow-up times. The GLM will also be used as a multivariate analysis to assess the influence of the treatment on the follow-up evolution of all the clinical scores and objective measures performed. The mixed linear regression model (MLM) will be used to assess whether PRP effects on the primary outcome at 12 months will be moderated by age, body mass index, and Kellgren and Lawrence grade. The between-group differences of continuous, normally distributed and homoscedastic data will be compared for their means using the analysis of variance (ANOVA). Nonnormal data will be compared using the Mann-Whitney U test.

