## Method/design

### Trial design

The allogeneic PRP injection for knee OA study is a prospective, randomized, double-blind, placebo-controlled trial design. This study protocol follows the recommendations of the SPIRIT Statement (supplement 1) [13] for clinical trial protocols elaboration and is reported according to the CONSORT Statement (supplement 2) [14]. The trial will be conducted at The First Affiliated Hospital of Soochow University, which is one of the three national clinical research centers for hematologic disease in China. The primary endpoint for the analysis of outcomes is 12 months after baseline assessment. The trial is registered at the Chinese Clinical Trial Registry with a number of ChiCTR2100048624 and follows the World Health Organization’s guidelines.

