### Outcome measures

Study outcome measures are presented in Table 1. The primary endpoint measure are 12-month change in knee pain and function scores.i.Knee pain and function score: this will be measured at baseline, 1-, 3-, 6- and 12-month using the Western Ontario and McMaster Universities (WOMAC) Osteoarthritis Index with terminal descriptors ‘mild OA (score <32)’, ‘moderate OA (score 32~48)’ and ‘severe OA (score >48)’. This was chosen because it has well-established clinimetric properties in knee OA and established minimal clinically important differences, and is a recommended measure for knee OA RCTs from the Osteoarthritis Research Society International [16–18].

The following secondary outcome measures will also be collected:i.Health-related quality of life: this will be measured at baseline, 1-, 3-, 6- and 12-month using the short-form 36-item health survey questionnaire (SF-36) instrument [19, 20]. The SF-36 is divided into 8 fields, with higher scores indicating better quality of life.ii.Overall knee pain score during activities of daily living (using an 11-point VAS): this will be measured at baseline, 1-, 3-, 6- and 12-month. The VAS is to indicate the degree of pain in a total of 11 numbers from 0 to 10; 0 means no pain and 10 means worst pain with high reliability. The patient chooses a number to represent the degree of pain according to his pain.iii.Lysholm knee scoring scale: this will be measured at baseline, 1-, 3-, 6- and 12-month. The Lysholm knee scale demonstrated overall acceptable psychometric performance for outcomes assessment of various chondral disorders of the knee. This makes up for the shortcomings of the WOMAC score and established minimal clinically important differences with high reliability [17, 21].iv.MRI-derived measurements: an MRI scan of the target knee will be performed at baseline and 12-month using a 3 T whole-body system with a dedicated extremity coil and a T1-weighted fat-suppressed 3D gradient recall acquisition sequence.

MRI osteoarthritis knee score (MOAKS): an OA-specific semi-quantitative tool evaluating multi-feature joint changes associated with OA [22]. We will assess the following subscores:

Meniscal morphology: any region worsening at 12-month; scored as yes or no.

Intercondylar synovitis incorporating synovitis and effusion: worsening at 12-month; scored as yes or no.

Whole knee effusion: categorized as worsened, no change, or improved.

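### The trial is sized for one 12-month test at alpha 0.05, but the primary analysis names a Sidak correction in a four-visit model without exempting the 12-month contrast; on the natural reading power is about 77%, not 90%

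*Protocol article*

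**What the plan says.** All places are in the protocol article.

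- **Trial design** fixes one primary time point: "The primary endpoint for the analysis of outcomes is 12 months after baseline assessment". The Abstract and the Discussion also give WOMAC at 12 months as the primary outcome.
- **Sample size calculations** uses that single time point: "The sample size calculation is based on the primary outcome measure, the WOMAC score at 12-month". The target is "a 11.5 points reduction in WOMAC total score was considered as the minimum difference to be detected between the groups", and the assumed SD is 16. With alpha 0.05 and power of at least 90%, "we determined a theoretical minimum sample size of 84 patients". Allowing for 15% dropout, this becomes 50 per group. No allowance for multiple comparisons is mentioned.
- **Statistical analysis** sets a general rule of two-sided tests at 0.05.
- **Primary outcomes analysis** then says, of the between-group difference in WOMAC, "we will use a repeated measurement general linear model (GLM) with Sidak test for multiple comparisons". The next sentence puts the changes at 1, 3, 6 and 12 months into the model, in order to examine differences at the various follow-up times. In that section 12 months is singled out only for the moderator analysis by age, body mass index and Kellgren-Lawrence grade.

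**The concern.** The sizing and the analysis do not describe the same test. The sizing pays for one comparison at 0.05. The analysis section describes a multiplicity-adjusted set of between-group comparisons on the same outcome and does not say that the 12-month comparison stands outside the adjustment.

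The Sidak family is not defined, but the text points one way. The Sidak phrase sits in the sentence about the between-group difference. Two arms give only one pair of groups, so several between-group comparisons on one outcome can arise only from the visits, and the following sentence lists four. Nothing in the article restricts Sidak to the visits before 12 months. A family of within-group comparisons over time would not fit the stated purpose of the sentence.

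At stake is a real 11.5-point effect at 12 months that could be missed because alpha was spent on visits that are not primary. The alpha for the primary claim also stays open to interpretation, and it should be settled before the data are unblinded.

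**Working it through.** **Inputs.** From Sample size calculations: difference 11.5, SD 16 (not stated whether of the 12-month score or of the change), alpha 0.05, power at least 90%, 84 evaluable, 15% dropout, 50 per group. From Randomization procedures: 1:1 allocation. From Statistical analysis: two-sided tests. From Primary outcomes analysis: four follow-up visits. The assumption that the article does not state is that the Sidak family is the four between-group visit contrasts.

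**Step 1: reproduce the plan's figure.** Standardised difference = 11.5/16 = 0.719. For n per arm the noncentrality is 11.5 / (16 × √(2/n)); for n = 42 this is 3.29.

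- Two-sample t-test (noncentral t), two-sided 0.05: power is 89.5% with 41 per arm and 90.2% with 42. The smallest n reaching 90% is therefore 42 per arm, or 84 in total, which is exactly the stated figure.
- Normal approximation: 41 per arm, 82 in total.
- Dropout: 84 / (1 − 0.15) = 98.8, so 99, rounded to 100.

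The 84 is thus the size of a single unadjusted 12-month comparison.

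**Step 2: the level per test under Sidak.** For k comparisons the level is 1 − (1 − 0.05)^(1/k). For k = 4 it is 1 − 0.95^(1/4) = 0.0127.

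**Step 3: power of the 12-month contrast at 42 per arm, by family size (t-test).**

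| Comparisons in the family | Level per test | Power |
|---|---|---|
| 1 | 0.0500 | 90.2% |
| 2 | 0.0253 | 84.3% |
| 3 | 0.0170 | 80.2% |
| 4 | 0.0127 | 77.0% |
| 5 | 0.0102 | 74.5% |

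For four comparisons the normal approximation gives 78.9%. If all 50 per arm are evaluable, power at 0.0127 is 85.2% (t-test) or 86.5% (normal).

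**Step 4: the size needed for 90% at 0.0127.** The t-test needs 57 per arm, 114 evaluable; 114 / 0.85 = 134.1, so 135 randomised, or 136 for equal arms. The normal approximation needs 56 per arm, 112 evaluable; 112 / 0.85 = 131.8, so 132 randomised.

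**Step 5: what the repeated-measures model could give back.** These powers use the article's simple two-group comparison with SD 16. A gain from the model depends on the within-patient correlation, which is not given. As a yardstick only: with 42 per arm, the effective SD would have to fall from 16 to about 14 to return to 90% at 0.0127 (normal approximation, 89.9%).

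**The case against.** The strongest reply is that the loss of power is conditional. The article never says which comparisons Sidak covers. If the 12-month contrast is tested alone at 0.05, with Sidak kept for the other visits, 84 patients and 90.2% power stand. The same section also says that between-group differences in suitable data are compared by ANOVA; for two groups this is equivalent to the t-test behind the 84. And a statistical analysis plan, which is not shown, may define the family.

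Much of this stands. The 77% cannot be stated as a fact about the trial. But the ANOVA sentence is tied to no outcome or visit, so it does not settle which test decides. Nor is this merely a detail left to a later document: the article itself states both an unadjusted sizing and an adjusted primary analysis, and as written they do not match.

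Two stronger readings are tempting, and neither is supported:

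- *That type I error for the primary claim is uncontrolled.* If Sidak did not span the visits, a reader might compute 1 − 0.95^4 = 18.5% as the false-positive risk. That is the chance of at least one false-positive visit if the visits were independent, which repeated scores from the same patients are not. The Abstract, Trial design, Sample size calculations and Discussion all fix 12 months as primary, so a significant result at 1, 3 or 6 months would not be the primary claim.
- *That the primary outcome itself is unclear because Outcome measures speaks of scores in the plural.* The same paragraph goes on to a single WOMAC item, and Sample size calculations specifies WOMAC total.

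**Conclusion.** The mismatch is real, but its size depends on the reading. Sample size calculations assumes one 12-month test at two-sided 0.05, while Primary outcomes analysis attaches Sidak to the between-group comparison in a four-visit model and does not exempt 12 months. On the natural reading, power for the 12-month contrast is about 77% with 42 evaluable per arm and about 85% with 50. This assumes a difference of 11.5, SD 16, a four-contrast family and no precision gain from the model. If 12 months is tested alone, the stated 90% is correct. The documents therefore do not show that the trial is underpowered; they show that the stated power is secure on only one of the available readings, and not on the one that the wording suggests.

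**What to change.** State in Primary outcomes analysis that the single primary test is the between-group difference in change from baseline in WOMAC total at 12 months, estimated from the same repeated-measures model and tested at two-sided alpha 0.05 without multiplicity adjustment. State that the contrasts at 1, 3 and 6 months are secondary and that Sidak applies to those only. The stated sample size and power then agree with the analysis.

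If the sponsor prefers to keep Sidak over all four visits, Sample size calculations should give the power for the 12-month contrast as about 77% with 84 evaluable patients.

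The first option costs two sentences and no extra patients. Its downside is that a result at an earlier visit can no longer carry the primary claim, which is consistent with the primary time point that the article already names. Either change should be made and dated before unblinding.

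### The primary model analyses change in WOMAC with no baseline WOMAC covariate named, which gives up power, and the plan does not say whether the SD of 16 belongs to the score or to the change

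*Protocol article*

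**What the plan says.** - **Primary model.** The Primary outcomes analysis section tests the treatment effect on WOMAC with a repeated-measures GLM and Sidak comparisons: "Changes from baseline to all follow-up time points (1-, 3-, 6- and 12-month) will be included in the model". Baseline WOMAC is not named as a covariate. The section does name age, body mass index and Kellgren-Lawrence grade as moderators, and the Secondary outcomes analysis section names adjustment variables for MRI outcomes.
- **Baseline data.** Table 1 and the Outcome measures section schedule WOMAC at baseline and at all four follow-up visits.
- **Sample size.** "The sample size calculation is based on the primary outcome measure, the WOMAC score at 12-month". The target is worded as follows: "a 11.5 points reduction in WOMAC total score was considered as the minimum difference to be detected between the groups", with an SD of 16. The Abstract and the Outcome measures section define the primary outcome as 12-month change.
- **Other tests.** The primary analysis section ends with ANOVA for normal, homoscedastic data, and then: "Nonnormal data will be compared using the Mann-Whitney U test". The Statistical analysis section, in its paragraph on baseline characteristics, adds: "Normality will be confirmed using the Kolmogorov-Smirnov test".

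**The concern.** A raw change score subtracts the whole baseline value. A baseline-adjusted model subtracts only the part that predicts the 12-month value. When r is below 1, subtracting all of it adds noise, and a chance baseline difference between the arms is over-corrected. With baseline WOMAC already collected, adjustment gains power at no cost.

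The sample size section makes this more than a matter of taste. It ties its SD to the 12-month score, but the model analyses change. These two quantities have the same SD only at r = 0.5 (with equal SDs at the two times). Whether the planned analysis has the stated 90% power may therefore depend on a correlation that the protocol never gives.

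There is a smaller matter. Three procedures (GLM, ANOVA, Mann-Whitney) stand under the primary analysis with nothing to say which one yields the primary result. Mann-Whitney gives no mean difference to compare with 11.5 points.

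**Working it through.** **Inputs.** Difference 11.5, SD 16, two-sided alpha 0.05, power at least 90%, 84 evaluable (42 per arm), 15% dropout and 50 per arm enrolled, all from the Sample size calculations and Statistical analysis sections. The correlation r is an assumption, shown from 0.3 to 0.7. Equal SDs at baseline and 12 months are also assumed. Power is for a two-sample t comparison at 12 months, as an approximation to the planned four-visit GLM and without the Sidak adjustment.

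**Step 1: the plan's own figure.** Standardised difference 11.5/16 = 0.719. The t-based formula gives 41.66, so 42 per arm and 84 in total, with 90.2% power. Dropout: 42/0.85 = 49.4, so 50 per arm. The stated figures reproduce as an unadjusted two-group comparison with SD 16.

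**Step 2: SD 16 is the SD of the score.** SD of change = 16√(2(1−r)). Baseline-adjusted residual SD = 16√(1−r²).

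| r | SD of change | Power, change, 42/arm | Power, change, 50/arm | Adjusted SD | Power, adjusted, 42/arm |
|---|---|---|---|---|---|
| 0.3 | 18.93 | 78.6% | 85.3% | 15.26 | 92.7% |
| 0.4 | 17.53 | 84.4% | 90.1% | 14.66 | 94.4% |
| 0.5 | 16.00 | 90.2% | 94.5% | 13.86 | 96.4% |
| 0.7 | 12.39 | 98.8% | 99.6% | 11.43 | 99.5% |

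Solving for 90% power with change scores gives r = 0.496 at 42 per arm and r = 0.397 at 50 per arm. The number per arm needed for 90%, change score against adjusted, is 58 against 39 at r = 0.3, 42 against 32 at r = 0.5, and 26 against 22 at r = 0.7.

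**Step 3: SD 16 is the SD of change.** Change-score power at 42 per arm is 90.2% whatever r is. The adjusted SD is 16√((1+r)/2):

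| r | Adjusted SD | Power, adjusted, 42/arm |
|---|---|---|
| 0.3 | 12.90 | 98.1% |
| 0.5 | 13.86 | 96.4% |
| 0.7 | 14.75 | 94.2% |

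**Step 4: efficiency under either reading.** The variance ratio, change to adjusted, is 2(1−r)/(1−r²) = 2/(1+r). That is 1.54, 1.33 and 1.18 at r = 0.3, 0.5 and 0.7.

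**Step 5: does a switch to Mann-Whitney cost anything?** Under normality, with relative efficiency 0.955, Mann-Whitney has about 89.6% power against 90.9% for the comparison of means (both by normal approximation). A simulation of the switch alone (42 per arm, 2,000 trials, change scores) gave 91.5% power with the switch and 91.6% without it for normal data. With skewed (gamma, shape 2) residuals at r = 0.5 it gave 91.8% and 89.7%. In a separate simulation of 3,000 trials, type I error stayed near 5%. How often the switch occurs depends on a detail that the protocol does not give. With a Lilliefors-corrected test in each arm it was about 10% of trials for normal data and about 50% for skewed data. With the uncorrected Kolmogorov-Smirnov test it was 0% and about 2%.

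**The case against.** The strongest reply is that this is a matter of efficiency, not validity. Under 1:1 randomization, change scores estimate the treatment effect without bias. That stands, and nothing here says that the planned analysis is invalid.

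A reader might infer from step 2 that the stated 90% power fails outright unless r is at least 0.5. The protocol does not support that. The threshold needs 16 to be the SD of the score and exactly 42 evaluable per arm. The sample size section does name the 12-month score, but it words the target as a reduction, and the primary outcome is defined elsewhere as change. On the change reading the power does not depend on r. With all 50 per arm retained, the threshold falls to about 0.4. The studies behind the SD are not available to settle the matter.

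A reader might also infer that a normality test decides which estimand becomes the primary result. That goes too far. The Kolmogorov-Smirnov sentence closes the paragraph on baseline characteristics, the GLM is stated without condition, and nothing says that Mann-Whitney replaces it. Step 5 shows no material loss of power or type I error even if it does. What remains is that the role of these tests is unclear.

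Finally, the absence of a baseline covariate is read from silence in a condensed article, and covariate lists often sit in an SAP. This has some weight. Against it, the article states the model and its change-score response positively, and it names covariates where the authors want them.

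**Conclusion.** The point holds as an avoidable loss of efficiency joined to an ambiguous SD. Baseline adjustment has more power than change scores under both readings of the SD and at every r shown. At 42 per arm it gives 92.7% to 99.5% for r from 0.3 to 0.7 if 16 is the SD of the score, against 78.6% to 98.8% for change scores. If 16 is the SD of change, it gives 94.2% to 98.1% against 90.2%. Adjustment therefore keeps power above 90% across the assumed range whichever SD was meant, and removes the dependence on that ambiguity. The figures rest on the assumed r, equal SDs at the two times, and the t approximation at 12 months. The unclear place of ANOVA and Mann-Whitney is a lesser matter of definition: they need a stated role, because a rank test cannot report the difference on which the trial was sized. The change is worth making, but the trial does not fail without it.

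**What to change.** - Add baseline WOMAC, with baseline-by-visit terms, to the primary repeated-measures model.
- Name the 12-month adjusted mean difference with its 95% CI as the single primary result, to be read against 11.5 points, whatever a normality test shows.
- Keep Mann-Whitney as a sensitivity analysis and say so. Either give ANOVA a stated role or drop it from the primary section.
- Treat VAS, Lysholm and SF-36 in the same way, each with its own baseline value.
- State in the sample size section whether 16 is the SD of the 12-month score or of the change and, if it is of the score, what correlation is assumed.

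The cost is wording only. The baseline values are already in the assessment schedule, and no further patients, visits or data are needed.

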### Secondary outcomes analysis

To test for the effect of treatment on between-group differences in secondary outcomes, we will also use the repeated measurement general linear model (GLM) with the Sidak test for multiple comparisons. Changes from baseline to all follow-up time points will also be included in the model. The statistical analysis method is similar to the primary analysis. MRI-derived measurements will be compared between groups using appropriate models, adjusting for age, sex, body mass index, and the stratifying variables. The success of blinding will be assessed using the James Blinding Index [26].

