### Randomization procedures

Randomization is centralized, and participants will be randomly allocated in a 1:1 ratio. An independent statistician will provide a computer-generated randomization list, using a permuted block design with block sizes of 4 and 6. The sequence is concealed by the use of a computer interface implemented in the electronic case report form. The patients, treating physicians and coordinating researchers will all be blinded to the allocation of the intervention. A study nurse will have access to the randomization result and the allocated intervention.

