## Discussion

This is a prospective, randomized, double-blind, placebo-controlled trial evaluating the efficacy and safety of intra-articular injection of allogeneic PRP from blood donors in patients with knee OA combined with hematologic blood dyscrasias with platelet dysfunction who are unsuitable for autologous PRP therapy. The primary outcome is the WOMAC score at 12-month. Our study will also evaluate the long-term efficacy of allogeneic PRP for up to 5 years.

Autologous PRP has been shown to alleviate the symptoms of patients suffering from knee OA and allogeneic PRP has been proven to be safe and effective in the treatment of osteoarthritis, rotator cuff disease, refractory wounds and other medical fields [3, 9–12]. In the absence of effective evidence-based non-surgical interventions for patients with knee OA combined with hematologic diseases with platelet dysfunction, allogeneic PRP would fulfill a clear clinical need. There was only one preliminary study on the efficacy of allogeneic PRP for knee OA with short follow-up periods, no control group, and low evidence [12]. In addition, all PRPs used for injection in the present study are from the same healthy donor at the same time and prepared with the same system. This avoids confounding factors and high risk of bias.

A positive study outcome is that allogeneic PRP could be used as a non-surgical intervention to treat patients with knee OA who are unsuitable for autologous PRP therapy. A negative outcome will prevent the widespread use of a non-efficacious treatment.

This study has potential limitations. First, the generalizability of results to other PRP products and treatment regimens remains unknown. All PRP products differ in their production method and content, and different treatment regimens regarding dose, timing and number of injections are used in clinical practice. However, we prepare PRP using commercial kits by standardized procedures and analyzed related components. Second, this study will not control for variations in physical therapies between the two groups. Throughout the trial, the exercise therapy and lifestyle will be registered. Third, the population recruited is from a single center. However, as our center is one of the three national clinical research centers for hematologic disease in China, it will help us screen a homogenous group of participants better.

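### The MRI models adjust for stratifying variables that the protocol article never names, so one term of the adjustment set is undefined

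*Protocol article*

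**What the plan says.** The Secondary outcomes analysis section of the protocol article gives the MRI analysis in one sentence: the two groups are to be compared on the MRI measures, "adjusting for age, sex, body mass index, and the stratifying variables". The model type is left open, but the covariates are stated.

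The Randomization procedures section says: "Randomization is centralized, and participants will be randomly allocated in a 1:1 ratio". An independent statistician generates the list, "using a permuted block design with block sizes of 4 and 6". No stratification factor is given there. The Discussion adds that "the population recruited is from a single center".

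On the MRI data, the Outcome measures section states that "an MRI scan of the target knee will be performed at baseline and 12-month", so a baseline value exists for every feature scored. Table 1 also lists age, gender, BMI and Kellgren-Lawrence grade as baseline descriptors.

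**The concern.** The MRI sentence presupposes particular strata. The randomisation section is detailed enough to give block sizes, yet supplies none. Either it leaves out strata that were used, or the analysis section carries a term that belongs to no part of this design. Each is an error, and a reader of the article cannot tell which one occurred.

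The consequence is modest but real. If strata were used, the analysis should reflect them; leaving balanced prognostic factors out of a linear model usually makes its standard errors too large. If none were used, the article leaves part of the covariate list to be settled later, on top of a model type that is already open. For yes/no MRI outcomes analysed by logistic regression (my assumption, since the article names no model), the covariate set also affects what the odds ratio means, because adjusted and unadjusted odds ratios differ even without confounding.

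A related weakness is that the covariate list omits the baseline value of the MRI feature being analysed, although that value is collected.

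**Working it through.** No figure in the article bears directly on this point, so the check is mainly a comparison of sections.

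**1. Is the sample size involved?** Inputs from Sample size calculations and Statistical analysis: difference 11.5, SD 16, two-sided α = 0.05, power 90%, dropout 15%.
- Normal approximation: n per arm = 2 × (1.96 + 1.2816)² × (16/11.5)² = 2 × 10.51 × 1.936 = 40.7, rounded up to 41, or 82 in total.
- t-test version: 41.66, rounded up to 42 per arm, or 84 in total. This is the article's figure.
- After dropout: 42/(1 − 0.15) = 49.4, rounded up to 50 per group, also as stated.

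No covariate or stratum enters this calculation, so it stands whichever section is corrected.

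**2. Does each adjustment term have a referent?**

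| Term in the MRI sentence | Defined or collected? |
|---|---|
| Age | Yes, Table 1 |
| Sex | Yes, Table 1 (gender) |
| Body mass index | Yes, Table 1 |
| Stratifying variables | No section names any |

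Three of the four terms can be applied as written. Site cannot fill the gap, because there is one centre. Kellgren-Lawrence grade is not offered as a stratum either. It appears as an eligibility range (grades 1–3), as a baseline descriptor, and in the question whether the WOMAC effect is "moderated by age, body mass index, and Kellgren and Lawrence grade". The Primary outcomes analysis section does not mention strata at all.

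**3. Which MRI outcomes already use baseline?** From Outcome measures:
- Defined as change: meniscal morphology ("Meniscal morphology: any region worsening at 12-month; scored as yes or no"), intercondylar synovitis (worsening), whole-knee effusion (worsened, unchanged, improved), bone marrow lesion size (progression, 0–3 per region), medial cartilage defects (progression by at least 1).
- Described as a level at both scans: the cartilage defect score, 0–4 per region.

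For the level score, a linear model that includes baseline reduces residual variance by the factor 1 − ρ², where ρ is the within-arm correlation between baseline and 12 months. The article gives no ρ, so I put no number on the gain. For the change outcomes the scale limits matter: a region already at 3 for lesion size, or at 4 for cartilage, cannot get worse, and a feature at 0 cannot improve. A baseline covariate lets the model account for this.

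**The case against.** The strongest defence is that this is a condensed article. A full protocol or analysis plan may define the strata, three of the four terms are clear, and the article has the analysis done by a blinded statistical expert. That is a fair reason not to fault the open model type. It does not remove the mismatch, because the article commits to a term that its own design section does not supply.

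Several stronger readings are tempting but go beyond the document:

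- *Randomisation was not stratified.* This is inferred from silence. The article names no strata, but it does not say there were none.
- *The MRI model cannot be fitted.* The set cannot be applied exactly as written, but a model with age, sex and body mass index can be fitted.
- *The analyst will choose covariates after seeing the data.* The article leaves room for this but does not show it, and an unseen analysis plan may close the gap.
- *Leaving out baseline MRI invalidates the comparison.* Randomisation protects against systematic bias, and most MRI outcomes are already defined relative to baseline. The omission alone is a detail an article may leave to the analysis plan, so the covariate is a recommendation and not a second contradiction.
- *Kellgren-Lawrence grade must be balanced or adjusted for.* With 50 per arm and an assumed 40% at grade 3, the chance difference between arms has SD √(0.4 × 0.6 × 2/50) = 0.098, so about 1 trial in 20 would differ by more than 1.96 × 9.8 = 19 percentage points. Assuming 20% to 50% gives SDs of 8 to 10 points and limits of 16 to 20. No section gives the proportion, and the figure describes ordinary chance imbalance under simple block randomisation. It does not measure the effect of an undefined covariate. The plan asks whether grade moderates the WOMAC effect; it does not treat grade as an established modifier.

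**Conclusion.** The inconsistency holds and should be corrected. It affects one term of four in the adjustment set for the secondary MRI outcomes. It does not reach the primary WOMAC analysis, the other clinical scores or the sample size, and it has no computable effect on any MRI estimate from what is published.

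This conclusion rests on the article alone. It would be resolved if the full protocol or analysis plan names the strata, although the article's two sections would still need to be aligned. Baseline adjustment is worth adding at the same time because it is almost free. The case is strongest for the cartilage defect level scores and weaker, though still reasonable, for outcomes already defined as change.

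**What to change.** Before the allocation is unblinded, make the two sections agree:

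1. **If strata were used:** name them, with their categories, under Randomization procedures, and keep them in the MRI models.
2. **If no strata were used:** delete the reference to stratifying variables from the MRI sentence.
3. **In either case:** add the baseline value of the same MRI feature to age, sex and body mass index. For regional scores, use the baseline score of the same region.
4. **Optional:** add baseline Kellgren-Lawrence grade, stated in advance. With 50 per group and some yes/no outcomes, the list should stay short, since sparse outcomes support few covariates.

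Regenerating the randomisation list with strata is not required. The cost is one or two sentences, with no new measurements and no change in sample size. The Ethics and dissemination section says that protocol revisions are documented in the trial registry, so the clarification can be recorded there.
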